## Abstract

**Background:**

The optimal approach for patients with gallbladder stones and intermediate risk of choledocholithiasis remains undetermined. The use of endoscopic retrograde cholangiopancreatography for diagnosis should be minimized as it carries considerable risk of postprocedural complications, and nowadays, less invasive and safer techniques are available.

**Objective:**

This study compares the two management strategies of endoscopic ultrasound before laparoscopic cholecystectomy and intraoperative cholangiography for patients with symptomatic cholecystolithiasis and intermediate risk of choledocholithiasis.

**Methods:**

This is a randomized, active-controlled, single-center clinical trial enrolling adult patients undergoing laparoscopic cholecystectomy for symptomatic gallbladder stones with intermediate risk of choledocholithiasis. The risk of choledocholithiasis is calculated using an original prognostic score (the Vilnius University Hospital Index). This index in a retrospective evaluation showed better prognostic performance than the score proposed by the American Society for Gastrointestinal Endoscopy in 2010. A total of 106 participants will be included and randomized into two groups. Evaluation of bile ducts using endoscopic ultrasound and endoscopic retrograde cholangiography on demand will be performed before laparoscopic cholecystectomy for one arm (“endoscopy first”). Intraoperative cholangiography during laparoscopic cholecystectomy and postoperative endoscopic retrograde cholangiopancreatography on demand will be performed in another arm (“cholecystectomy first”). Postoperative follow-up is 6 months. The primary endpoint is the length of hospital stay. The secondary endpoints are accuracy of the different management strategies, adverse events of the interventions, duct clearance and technical success of the interventions (intraoperative cholangiography, endoscopic ultrasound, and endoscopic retrograde cholangiography), and cost of treatment.

**Results:**

The trial protocol was approved by the Vilnius Regional Biomedical Research Ethics Committee in December 2017. Enrollment of patients was started in January 2018. As of June 2020, 66 patients have been enrolled.

**Conclusions:**

This trial is planned to determine the superior strategy for patients with intermediate risk of common bile duct stones and to define a simple and safe algorithm for managing choledocholithiasis.

**Trial Registration:**

ClinicalTrials.gov NCT03658863; https://clinicaltrials.gov/ct2/show/NCT03658863.

**International Registered Report Identifier (IRRID):**

DERR1-10.2196/18837

## Introduction

Gallbladder stones can be silent or symptomatic. This statement is also valid when speaking about choledocholithiasis, which involves stones situated in the common bile duct (CBD). About 10% to 18% of people undergoing cholecystectomy for gallstones have concomitant CBD stones [1]. Untreated choledocholithiasis can lead to acute biliary pancreatitis, acute ascending cholangitis, and secondary sclerosing cholangitis; thus, it is essential to diagnose and treat it on time. Endoscopic retrograde cholangiopancreatography (ERCP) became a prominent diagnostic method for CBD stones since its introduction to clinical practice in the 1970s [2]. Later on, it was agreed that use of ERCP for diagnostic reasons should be minimized and that it should not be used for first-line diagnostics as it carries a considerable risk (5% to 10%) of postprocedural complications [3]. It has been noticed that adverse events occur more often in patients with low risk of choledocholithiasis [4]. The possibility to avoid using ERCP for diagnostic purposes came with the introduction of new less invasive diagnostic procedures, such as magnetic resonance cholangiopancreatography (MRCP), endoscopic ultrasound (EUS), and intraoperative cholangiography (IOC) during cholecystectomy. Therefore, in the 2000s, a discussion about more careful patient selection for ERCP began, as it should be considered only in those with high probability of demand for therapeutic interventions (ie, stone removal), and patients with intermediate risk for choledocholithiasis should undergo additional investigation.

The most frequently used system to evaluate the risk of choledocholithiasis was proposed in 2010 by the American Society for Gastrointestinal Endoscopy (ASGE) [5]. It already stratifies the probability of CBD stones into low, intermediate, and high risk groups, and it suggests noninvasive investigations for the intermediate risk group, although its predictive value is not completely satisfying [6-10]. These results encourage the development of more accurate prognostic systems.

At the Center of Abdominal Surgery of Vilnius University Hospital Santaros Klinikos, an original prognostic index (Vilnius University Hospital Index [VUHI]) is being used for the prediction of choledocholithiasis risk before laparoscopic cholecystectomy (LC). Recently, we evaluated its accuracy and determined new threshold values for low, intermediate, and high risk groups [11]. The intermediate risk group (risk for choledocholithiasis of 25%-75%) would benefit from additional examination before ERCP. EUS and IOC are less invasive procedures with high accuracy for identifying CBD stones. These procedures will be applied for patients with intermediate risk of CBD stones and will help to decide if ERCP is indicated.

We aim to compare EUS as the first diagnostic biliary intervention to LC with IOC in patients with intermediate risk of choledocholithiasis in order to evaluate the accuracy, technical success, and safety of these two management strategies.

The hypothesis is that LC with IOC (“cholecystectomy first” strategy) will decrease both the length of hospital stay and morbidity by lessening the number of endoscopic investigations (EUS and ERCP) and thus the number of possible complications of ERCP, as well as decreasing the complications related to delayed cholecystectomy.

## Methods

### Recruitment

This study is a single-center, randomized, active-controlled trial comparing EUS and IOC for finding CBD stones in patients with intermediate risk of choledocholithiasis. Participants will be enrolled and the trial will be carried out at Vilnius University Hospital Santaros Klinikos, a tertiary referral center. All patients with planned LC due to gallstone disease will be evaluated for trial eligibility.

Ethical approval has been obtained from the Vilnius Regional Biomedical Research Ethics Committee (approval protocol number 158200-17-978-473).

The eligibility criteria are listed in Textbox 1 [12-14]. The trial will enroll patients with cholecystolithiasis aged 18 to 80 years, for whom LC is indicated and who have intermediate risk of choledocholithiasis. We will not include patients who are pregnant, morbidly obese (BMI >40), or severely ill (IV-VI class of the American Society of Anesthesiologists physical status classification, contraindications for general anesthesia or surgery). Additionally, patients with anastomosis in the upper gastrointestinal tract, known or suspected hepatitis of another origin (viral, toxic, etc), and other known cholestatic hepatopancreatobiliary disease will be excluded. We will rule out patients with known complications of gallstone disease, such as biliary pancreatitis, acute cholangitis, and acute cholecystitis (degree II-III, as defined in the Tokyo guidelines) [12,13].

Eligibility criteria.
**Inclusion Criteria**
Age 18-80 yearsSymptomatic cholecystolithiasis (stones in the gallbladder seen on imaging studies and causing episodes of biliary colic)Intermediate risk of choledocholithiasis (Vilnius University Hospital Index 2.6-6.9 and one of the following predictors: dilated common bile duct >6 mm, elevated total bilirubin >21 µmol/L, or suspected stone in the common bile duct [CBD] on ultrasound)
**Exclusion Criteria**
Acute cholangitis, as defined in the Tokyo guidelines 2013 [12]Moderately severe or severe biliary pancreatitis, as defined in the revised Atlanta classification [14]Acute cholecystitis (degree II-III), as defined in the Tokyo guidelines 2013 [13]Anastomosis in the upper gastrointestinal tractKnown cholestatic hepatopancreatobiliary disease (primary biliary cholangitis, primary sclerosing cholangitis, secondary biliopathy, tumor of the head of the pancreas or major papilla, or benign or malignant CBD stricture)Known or suspected hepatitis (viral, toxic, alcoholic, etc) or liver cirrhosisContraindications for general anesthesia or surgeryIV-VI class of the American Society of Anesthesiologists physical status classificationMorbid obesity (BMI > 40)PregnancyPatient refusal to participate in the study

### Elimination From the Trial

Patients will be omitted from the trial if the situation changes to incompatible with the trial protocol. This can happen because of the following reasons: a neoplastic condition is found at the time of management; the general status of the patient worsens owing to other health issues not related to cholelithiasis (eg, myocardial infarction) and the patient needs urgent interventions not included in the trial protocol; and LC is converted to open cholecystectomy before IOC in the “cholecystectomy first” arm. Additionally, if the patient refuses to further participate in the trial, all the patient’s data are eliminated and further follow-up is not carried out. Informed consent will be obtained from all study participants.

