### Statistical Analysis

The sample size was calculated in reference to collected data on the management of choledocholithiasis in the trial center Vilnius University Hospital Santaros Klinikos [11]. In our previous study, the mean treatment durations for different management strategy groups (LC-IOC first and ERCP first) were 5.37 and 7.13 days, with SDs of 2.5 and 2.8, respectively, and these findings were used to calculate the requested sample size. The program G*Power version 3.1.9.2 was used for calculations. It was calculated for a two-tailed *t* test for means of two independent groups. The significance level was selected to be .05, with a power of 0.8. The required sample size is 74 (37 valid participants in each of the two groups).

The endpoints in different management groups will be analyzed using the chi-square test or *t* test for independent means. Two-sided hypotheses are to be checked, and a *P* value <.05 will be considered statistically significant. If the distribution is nonnormal, a transformation, such as the logarithm or square root function, can be applied to obtain a normal distribution or nonparametric tests, such as the Mann-Whitney test, can be used. To evaluate the achieved power, a post-hoc power analysis calculation will be performed.
As for the primary outcome, a difference of 2 days of hospital stay will be considered clinically meaningful.

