### Outcomes

The primary endpoint is the length of hospital stay (duration from enrollment into the trial to discharge, in days).

The secondary endpoints are as follows:

1. Diagnostic accuracy of the different management strategies (proportion of correctly diagnosed [true positive and true negative] cases in the entire sample; time frame: 6 to 12 months).

2. Technical success of diagnostic and therapeutic biliary procedures (IOC, EUS, ERCP) (during the active treatment period). For IOC, successful cannulation and contrast media injection into the CBD are considered. For EUS, successful visualization of the CBD is considered. For ERCP, successful cannulation and contrast media injection into the CBD are considered. Successful CBD clearance is also considered.

3. Postoperative course and possible complications of treatment (time frame: up to 1 month). With regard to adverse events of endoscopic interventions and IOC, we consider (1) bleeding, hematemesis and/or melena, or hemoglobin drop >20 g/L; (2) perforation, evidence of air or luminal contents outside the gastrointestinal tract; (3) post-ERCP pancreatitis, new or worsening abdominal pain persisting for at least 24 h and requiring analgesics after ERCP in conjunction with an elevation in serum amylase or lipase levels greater than three times the normal upper limit [16,17]. We also consider assessment of the postoperative course by the Clavien-Dindo classification of surgical complications [18].

4. Cost of treatment (charges for diagnostic procedures, invasive procedures, surgery, and antibacterial treatment, if needed, as well as hospital charges).

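### The elimination rule can remove a patient with a serious perioperative event from the arm in which it occurred, because it asks whether the event relates to gallstones, not to trial treatment

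*Protocol article*

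**What the plan says.** All references are to the protocol article.

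- **Elimination From the Trial.** The governing sentence is "Patients will be omitted from the trial if the situation changes to incompatible with the trial protocol". One listed reason has two parts, both required. The first is a deterioration of a certain kind: "the general status of the patient worsens owing to other health issues not related to cholelithiasis (eg, myocardial infarction"). The second is a need for treatment that the protocol does not cover: "and the patient needs urgent interventions not included in the trial protocol". The section speaks of eliminating a patient's data only for patients who refuse further participation.
- **Outcomes, primary endpoint.** "The primary endpoint is the length of hospital stay (duration from enrollment into the trial to discharge, in days"). The clock starts at enrollment, before any trial procedure.
- **Outcomes, third secondary endpoint.** "Postoperative course and possible complications of treatment (time frame: up to 1 month"). Bleeding, perforation and post-ERCP pancreatitis are named as adverse events of endoscopy and IOC. The article then adds: "We also consider assessment of the postoperative course by the Clavien-Dindo classification of surgical complications". That assessment is not restricted to biliary causes.
- **Introduction.** The hypothesis is that the cholecystectomy-first strategy "will decrease both the length of hospital stay and morbidity by lessening the number of endoscopic investigations (EUS and ERCP").
- **Randomization and Data Protection; Blinding.** An investigator opens the envelope. The article describes participant, clinician and investigator as unaware of the arm only before enrollment.
- **Statistical Analysis.** The required sample size is expressed as valid participants, 37 per group.

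**The concern.** The rule acts after randomisation and is triggered by a bad clinical course. An infarction around general anaesthesia, endoscopy or laparoscopic surgery is unrelated to gallstones, yet it may be a consequence of the strategy being tested. Under one section the patient may be omitted. Under another, the same postoperative event would be graded as part of the complication endpoint.

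Two features turn this into a question of bias as well as tidiness. Relatedness would be judged by staff who know the arm. The arms also differ in exposure: the endoscopy-first arm has EUS, with ERCP under the same anaesthesia if stones are seen, and LC afterwards; the cholecystectomy-first arm has LC with IOC and adds ERCP only if stones are found. Losses need not balance.

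Both halves of the hypothesis, stay and morbidity, are exposed. An event before any procedure is not a postoperative complication, but its hospital days still belong to the primary endpoint.

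**Working it through.** **The plan's own figure.** Inputs from Statistical Analysis: the means and SDs "were 5.37 and 7.13 days, with SDs of 2.5 and 2.8, respectively", two-sided alpha 0.05, power 0.80.

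- Pooled SD = √((2.5² + 2.8²)/2) = 2.654.
- Standardised difference = (7.13 − 5.37)/2.654 = 1.76/2.654 = 0.663.
- The noncentral t calculation gives 36.7, so 37 per group and 74 in total (power 0.803).

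The stated 74 is reproduced and is not in dispute. The abstract's 106 participants, randomised 1:1, give 53 per arm.

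**How each kind of event is treated**

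| Event, if urgent non-protocol intervention is needed | Elimination section | Outcomes section |
|---|---|---|
| Infarction after enrollment, before any procedure | can be omitted | not a postoperative complication; days count in stay |
| Infarction after EUS/ERCP, before LC | can be omitted | not a named endoscopic event and not plainly postoperative; days count in stay |
| Infarction after LC | can be omitted, if the course is held incompatible with the protocol | graded by Clavien-Dindo; days count in stay |

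Hospital days are at stake in every row. The direct clash over complications is in the last row.

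**Size for hospital stay.** The documents give no event rate and no length of stay after such an event. Assume one patient with a stay L of 14 to 21 days. If the other patients in an arm of n average m, omitting that patient lowers the arm's mean by (L − m)/n.

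| Arm, with m | n = 53 | n = 37 |
|---|---|---|
| Cholecystectomy first, 5.37 | 8.63/53 = 0.16 to 15.63/53 = 0.29 | 8.63/37 = 0.23 to 15.63/37 = 0.42 |
| Endoscopy first, 7.13 | 6.87/53 = 0.13 to 13.87/53 = 0.26 | 6.87/37 = 0.19 to 13.87/37 = 0.37 |

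As a share of the 1.76-day planning difference, the first row is 9% to 17% at n = 53 (0.163/1.76 to 0.295/1.76) and 13% to 24% at n = 37 (0.233/1.76 to 0.422/1.76).

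The direction depends on the arm. With n = 37 and L = 21, suppose the analysed means are 5.37 and 7.13, so the reported difference is 1.76. Had the omitted patient been in the cholecystectomy-first arm, the difference with that patient retained would be 1.76 − 0.42 = 1.34. In the endoscopy-first arm it would be 1.76 + 0.37 = 2.13.

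**Size for complications.** One event is 1/53 = 1.9 or 1/37 = 2.7 percentage points of an arm.

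**Effect of retaining the patient on the SD.** Take n − 1 patients with mean 5.37 and SD 2.5, plus one assumed 20-day stay:

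SD² = [(n − 2)·2.5² + ((n − 1)/n)·(20 − 5.37)²]/(n − 1)

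- n = 37: (218.75 + 208.25)/36 = 11.86, so SD = 3.44.
- n = 53: (318.75 + 210.00)/52 = 10.17, so SD = 3.19.

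**The case against.** The strongest reply is that the section is about feasibility, not analysis. Read whole, it concerns patients who can no longer follow the pathway. It requires both an unrelated deterioration and urgent non-protocol intervention, so not every infarction or decline leads to omission. After the allocated procedures are finished, little may remain to be incompatible with. Data elimination is stated for refusal alone, which leaves room for retaining data in the other cases. The two sections can also be reconciled by treating events caused by treatment as complications and intercurrent illness as an other health issue.

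Much of this stands, and it limits the point. A reader might infer that the protocol orders these patients' data to be deleted; the text does not say so. A reader might also infer that any infarction after endoscopy is a complication the trial undertakes to count. Infarction is not among the named endoscopic events and enters only through the Clavien-Dindo assessment of the postoperative course, so an event between endoscopy and LC is not clearly covered.

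The reply does not remove the problem. The heading and the governing sentence both put the patient out of the trial. Nothing says that patients omitted for these reasons are analysed, and a sample size counted in valid participants fits their removal, though it does not prove it. The criterion as worded is relation to cholelithiasis. The reconciling reading needs relation to treatment, which the article does not state. An unseen analysis plan may define the analysis sets, but it would have to depart from a rule the article itself states.

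On size, the events should be uncommon: ASA classes IV to VI and contraindications to general anaesthesia are excluded, and age is capped at 80. The permitted transformation or Mann-Whitney test would also blunt one long stay.

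**Conclusion.** The point holds as a badly fixed rule. As worded, it permits post-randomisation loss of serious events and long stays, through a judgement that is not blinded and that uses the wrong criterion for a comparison of treatments. For an event after LC that meets both conditions, the Elimination and Outcomes sections pull in different directions.

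The effect is modest per patient: about 0.16 to 0.29 days of an arm's mean at 53 per arm, or 0.23 to 0.42 at 37, and 1.9 or 2.7 percentage points of a complication rate. The stay figures rest on an assumed stay of 14 to 21 days, other patients averaging 5.37 days, and one omission; how many would occur is unknown.

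A reader might go further and conclude that the rule favours cholecystectomy first, or that it would hide an excess of cardiac events. The documents do not support that. The direction depends on which arm has the events and cannot be known in advance. The planned sample size of 74 is unaffected as a calculation.

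**What to change.** Keep this reason only as a description of when a patient may leave the allocated pathway, or as the definition of a per-protocol sensitivity set. Then state that:

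- every randomised patient stays in the assigned arm for hospital stay, complications and cost;
- any deterioration after randomisation is recorded whatever its judged cause, and is graded by Clavien-Dindo when it falls in the postoperative course;
- a sensitivity analysis may leave out events judged unrelated to treatment.

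This concerns only who is analysed and changes nothing in patient care.

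The cost is a protocol amendment during enrolment (66 of 106 patients enrolled as of June 2020) and continued collection of discharge date, complications and charges for these patients. Retaining a long stay also widens the spread appreciably: one assumed 20-day stay raises an arm's SD from 2.5 to about 3.4 at n = 37 or 3.2 at n = 53. The transformation or Mann-Whitney test already allowed under Statistical Analysis can temper this. There is also some slack: at the planning means and SDs, 53 analysed per arm would give power of 0.92.

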### Randomization and Data Protection

Eligible patients who provide informed consent will be assigned to the groups “endoscopy first” or “cholecystectomy first” randomly, according to a premade sequence. The sequence is generated by a randomization website [15]. The sequence is created using block randomization of two elements A and B (“endoscopy first” and “cholecystectomy first”) in a ratio of 1:1. According to the sequence, sheets with group names are enclosed in opaque envelopes. Envelopes are numbered, and the envelope number is the patient number in the trial. When a new participant is enrolled, the topmost envelope is opened by one of the investigators and the participant is randomized into the specified group.

All collected data are coded, that is, every case receives an individual number. Only coded data will be employed for statistical analysis and publishing. Uncoded data are available only for researchers of the trial and, on special and reasonable request, for the coordination center for biomedical research of the institution and Biomedical Research Ethics Committee.

Data are processed and stored in an electronic database, and physical (“paper”) copies are stored at the trial center in accordance with procedures established by law.

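### Conversion to open surgery before IOC removes a randomised patient from the cholecystectomy-first arm only, which can bias length of stay toward the hypothesised winner

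*Protocol article*

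**What the plan says.** The section Elimination From the Trial opens with a general rule: "Patients will be omitted from the trial if the situation changes to incompatible with the trial protocol". It then lists the reasons.

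- Neoplasm: "a neoplastic condition is found at the time of management".
- Unrelated illness: "the general status of the patient worsens owing to other health issues not related to cholelithiasis", with a need for urgent interventions outside the protocol.
- Conversion: "LC is converted to open cholecystectomy before IOC in the" cholecystectomy-first arm.
- Refusal: "if the patient refuses to further participate in the trial, all the patient’s data are eliminated and further follow-up is not carried out".

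Only the conversion reason names an arm. The other three are worded for both.

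Allocation comes before any of these events. Under Randomization and Data Protection: "When a new participant is enrolled, the topmost envelope is opened by one of the investigators and the participant is randomized into the specified group". Under Procedure, cholecystectomy follows the endoscopic work-up in endoscopy-first, and all patients are to have the same four-port operation. Under Outcomes, the primary endpoint is the stay from enrolment to discharge, in days. The Statistical Analysis section states the target in terms of valid participants: "The required sample size is 74 (37 valid participants in each of the two groups"). The Introduction expects cholecystectomy-first to shorten stay and reduce morbidity, and the Discussion calls the study a superiority trial.

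**The concern.** Conversion can happen in either arm, because every patient is to be operated on laparoscopically. A conversion before IOC takes the patient out of cholecystectomy-first, whereas a comparable conversion in endoscopy-first leaves the patient in. The two analysed groups are then no longer the two randomised groups, and what separates them is an outcome of surgery.

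Nothing about the primary endpoint requires the omission. A converted patient still has an enrolment date and a discharge date, so the stay is fully observed. If conversion marks a difficult operation with a longer recovery, the rule trims long stays, complications and costs from one arm, and that arm is the one expected to win.

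A second effect concerns IOC alone. Technical success of IOC is defined as successful cannulation and contrast injection. A patient converted before IOC has achieved neither, yet leaves the denominator.

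**Working it through.** **The plan's own figure.** The Statistical Analysis section gives means of 5.37 and 7.13 days, SDs of 2.5 and 2.8, two-sided alpha 0.05 and power 0.80.

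- Difference: 7.13 − 5.37 = 1.76 days.
- Pooled SD: √((2.5² + 2.8²)/2) = √7.045 = 2.654. Standardised effect: 1.76/2.654 = 0.663.
- Noncentral t: 37 per arm gives power 0.803, and 36 gives 0.792. The stated 37 per arm (74 in total) is reproduced. The sample size is not wrong on this account.
- The Abstract plans 106 participants at 1:1, so 53 per arm.

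**Bias from the rule.** Let c be the share of cholecystectomy-first patients converted before IOC, e their excess stay in days over the rest of that arm, and m the mean of the rest.

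- Mean of all randomised: (1 − c)·m + c·(m + e) = m + c·e.
- Mean after omission: m.
- Bias: −c·e days, in favour of cholecystectomy-first if e > 0.

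The document gives neither c nor e, so both are assumptions. The rejection rates below assume that the arms have the same conversion rate and no true difference, that conversions leave only cholecystectomy-first, and that there are 53 per arm before omission. The closed form is a noncentral t with the SD held at 2.654. The simulation uses gamma-distributed stay (mean 6.25, SD 2.65), a t test and 20,000 runs.

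| c | e (days) | Bias (days) | Share of 1.76 | Error, closed form | Error, simulated |
|---|---|---|---|---|---|
| 2% | 3 | −0.06 | 3% | 5.2% | 5.3% |
| 5% | 3 | −0.15 | 9% | 5.9% | 6.1% |
| 5% | 5 | −0.25 | 14% | 7.6% | 7.1% |
| 10% | 3 | −0.30 | 17% | 8.7% | 8.6% |
| 10% | 5 | −0.50 | 28% | 15.5% | 13.8% |

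In the last row the simulation is lower because the extra days widen the SD in the arm that keeps its conversions: √(2.65² + 0.10 × 0.90 × 5²) = √9.27 = 3.04. Repeat simulations of that row gave 12.8% and 13.2%, so about 13% is a fair summary. Of the 13.8%, 13.6 percentage points are false wins for cholecystectomy-first, against a nominal 2.5. With 37 per arm the same scenario gives 10.8% by simulation.

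**Conversions after IOC.** The rule removes only conversions before IOC. Suppose half of a 10% conversion rate comes before IOC, with 5 extra days. The mean of all randomised is m + 0.50. After omission, 0.05/0.95 = 5.3% of those left are converted, and the mean is m + 0.26. The bias is −0.24 day, with a simulated error of 6.6%. For a 5% rate and 5 days, it is −0.12 day and 5.7%.

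**IOC technical success.** Assume 5 of 53 are converted before IOC and IOC succeeds in the other 48. The rule reports 48/48 = 100%. Counted over all allocated patients it is 48/53 = 91%.

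**The case against.** The strongest defence is that the article condenses a longer plan, and an analysis plan not shown could define an all-randomised set. A patient who never reached IOC also contributes nothing to its diagnostic accuracy, so leaving that patient out of an accuracy table is understandable. Neither argument rescues the rule. The difficulty is not a missing population definition: the article states an exclusion, ties it to one arm, and contains nothing that brings the patient back. An argument about accuracy does not carry over to length of stay, which is observed whether or not IOC took place.

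The objections about size do stand. No conversion rate or excess stay is given. At 2% conversion the effect is negligible. Conversions after IOC are not removed. The plan also allows a transformation or a Mann-Whitney test for non-normal data, which brings the worst tabulated case to about 10–11%.

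A reader might infer more than the document supports:

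- *All the elimination reasons are one-sided.* Only the conversion reason is.
- *Unequal detection of neoplasm adds to the same bias.* Preoperative EUS is done only in endoscopy-first, so any extra detection would remove patients from that arm. If they would have had long stays, the effect runs the other way. The document gives no rate.
- *The gap between 106 and 74 shows that 30% will be dropped.* 74/0.70 = 105.7 rounds up to 106, but the article does not explain the surplus, and it is no evidence about conversions.
- *Some of the 66 enrolled patients have already been removed.* The article reports only the enrolment count.

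**Conclusion.** The conversion rule is wrong as written. It excludes randomised patients after allocation, in one arm only, on an event that can occur in both, and it acts on the primary endpoint. The direction, toward cholecystectomy-first, rests on converted patients staying longer than others. That is plausible but not documented. The size is equally assumption-driven: from immaterial at low conversion rates to roughly half a day, more than a quarter of the planned 1.76-day difference, at the top of the range shown. The inflation of IOC technical success follows from that endpoint's definition whenever such a conversion occurs, unless every remaining IOC fails. It concerns a rate within one arm and is not a contrast between arms.

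The neoplasm, unrelated-illness and refusal reasons are also exclusions after randomisation and should be treated in the same way, but no direction of bias can be established for them. It would go too far to say that the primary result will be biased by a known amount.

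**What to change.** Reword Elimination From the Trial so that the listed events end protocol procedures only and do not remove the patient from the analysis. Then state the following.

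- Every randomised patient is analysed in the allocated arm for length of stay, complications and cost.
- Conversion before IOC counts as IOC not achieved in the technical-success endpoint, with stay, complications and cost kept.
- Any set without converted, neoplasm or intercurrent-illness cases is a sensitivity analysis only, with the same rule in both arms.
- Data collected up to withdrawal are kept unless the participant asks for erasure or the consent terms require it. At present the article says that "data are eliminated and further follow-up is not carried out" on any refusal.
- If any patient already enrolled was eliminated under this rule, that patient is included where consent allows.

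The cost is protocol wording, retrieval of a few hospital records and slightly larger variance from the long stays retained. The required 74 analysed patients do not change under the plan's own assumptions.
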